**Methods:**

Two mixed-methods randomized controlled trials will be conducted. In Study 1, participants will be randomly assigned to one of three groups (HIFT, MBSR, QG) using a 1:1:1 ratio. Psychological, cognitive, physical, physiological, and biological measures will be evaluated two weeks before and after the interventions. The interventions include three weekly sessions for 12 weeks. Subsequently, a follow-up will be conducted 12 weeks after the intervention to assess psychological well-being. Study 2 is a proof-of-concept study in which VR interventions will be co-designed with input from university students and professionals. Twelve participants from each study will also complete semi-structured interviews to explore their experiences and perceived impact.

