**Fig 2 pone.0328538.g002:**
[figure not shown]
Key variables of interest in the YoungFitT study. HIFT: High-Intensity Functional Training, MBSR: Mindfulness-Based Stress Reduction Therapy, QG: Qigong, VR: Virtual Reality, HRV: Heart Rate Variability.

The key hypotheses for this objective are: (1) All three interventions will positively affect psychological well-being and cognitive functions at 12 weeks compared to baseline, with each intervention showing a specific profile of outcomes (HIFT: more cognitive gains; MBSR: more psychological gains; QG: moderate benefits in both areas). These positive effects are expected to persist at the 12-week follow-up; (2) All interventions are expected to induce changes in physical components (increased physical activity and fitness status), mental components (enhanced mindful thinking and sleep quality), physiological stress markers (increased HRV), and microbial composition (increased diversity), which will mediate improvements in psychological well-being and cognitive outcomes; (3) Sociodemographic factors (sex and age) and individual factors (cognitive reserve and general intelligence) will moderate changes in outcomes from pre- to post-intervention.

**Study 2 focuses on VR-based physical exercise and mind-body interventions.** The primary objective of this proof-of-concept study is to test the feasibility and preliminary effectiveness of VR-based HIFT, MBSR, and QG interventions on the psychological well-being and cognitive functions of university students. The specific objectives of this study include: (1) Generating virtual environments for HIFT, MBSR, and QG interventions; (2) Evaluating the usability, acceptability, and feasibility of these VR interventions; (3) Studying the effectiveness of VR interventions as depicted in Fig 2; and (4) Exploring the effects and adherence of these VR-based physical exercise and mind-body interventions compared to non-VR interventions.

It is hypothesized that: (1) All VR interventions will positively affect psychological well-being and cognitive functions after 12 weeks, with each intervention displaying distinct outcomes (HIFT: cognitive gains; MBSR: psychological gains; QG: moderate benefits); and (2) VR-based interventions will yield better adherence and greater benefits compared to non-VR interventions.

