## Materials and methods

### Study design

The YoungFitT project is a prospective, three-arm, parallel, single-blinded RCT mixed-methods study planned to be conducted in two phases, as illustrated in Fig 3. Study 1 will begin first, followed shortly by Study 2. Both studies adhere to the SPIRIT guidelines [66] (See S1 File). The Faculty of Psychology at the University of Barcelona will lead this interdisciplinary project, integrating expertise in neuropsychology, sports science, and computer science. The study protocol has been registered at ClinicalTrials.gov (identifier: NCT06406283) and approved by the institution’s Bioethics Committee (IRB number: IRB00003099; protocol code: CER112327) on October 18, 2023 (See S2 and S3 Files). It also complies with the ethical standards outlined in the Declaration of Helsinki. Eligible participants who agree to take part in the study will provide written informed consent. A member of the research team will obtain the signed consent form prior to conducting any baseline assessments. Protocol amendments will be updated on ClinicalTrials.gov and shared with regulatory bodies if necessary.

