#### Study status and timeline.

Participant recruitment is anticipated to occur in three waves for Study 1 (February 2024, February 2025, and September 2025) and three waves for Study 2 (September 2025, December 2025, and February 2026), although this schedule may vary depending on study needs. Each recruitment wave will last approximately four months. Recruitment began on 5 February 2024 and is expected to be completed by February 2026. Data collection is actively being conducted and is anticipated to conclude by June 2026. We estimate that results will be analyzed and reported by August 2026.

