### Randomization

In Study 1, an independent researcher will use a software-generated random sequence to allocate participants into three groups at a 1:1:1 ratio for each wave (Fig 3). The randomization list will be securely generated and stored on a university server. While the research team will be aware of the allocation sequence, participants will remain unaware of their group assignment until the intervention. In Study 2, participants will be assigned to one of three intervention groups through sequential cohort assignment based on recruitment order. Potential biases in group composition will be mitigated by monitoring baseline characteristics across groups and adjusting for these in subsequent analyses. Outcome assessors will be blinded to group allocation through the use of coded identifiers to ensure unbiased assessments. To prevent unintentional disclosure, participants will be reminded not to discuss their group allocation during post-intervention assessments. To assess blinding success, outcome assessors will guess participants’ group assignments after the final evaluation. The proportion of correct guesses will be compared to the 33% chance level using a chi-square goodness-of-fit test with one degree of freedom. Data analysts will conduct analyses without access to group allocation information, thereby ensuring the integrity of the results.

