### Sample size

A power analysis was conducted using G*Power software (version 3.1.9.4) for a one-way ANOVA (fixed effects, omnibus) with three groups. Assuming a medium effect size (f = 0.25), α = 0.05, and a desired power of 0.80, the analysis yielded a required sample size of 159 participants, with a critical F-value of 3.054. To accommodate an expected dropout rate of 10%, the sample size was adjusted using the proportional method, resulting in a final target of 177 participants (59 per group). This adjustment ensures that statistical power remains adequate even if participant attrition occurs. Study 2 will include 45 participants (n = 15 per group) as part of a proof-of-concept trial intended for preliminary exploration. For Study 1, biological samples (fecal) will be collected from a randomly selected subgroup of 90 participants (30 per group) before and after the interventions. Furthermore, a subset of 24 participants (12 from each study) will be selected for the qualitative study using purposive sampling to capture diverse perspectives [67]. The sample size is based on previous studies [56,61,68] and evidence suggesting that qualitative inquiry often reaches data saturation with approximately 12 participants [69].

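### Study 2 is described as a randomised controlled trial, but its arms are assigned by recruitment order; if each cohort receives one arm, arm and calendar wave cannot be separated

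*Protocol article*

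**What the plan says.** The Methods paragraph of the abstract states: "Two mixed-methods randomized controlled trials will be conducted". Study design repeats the label for the whole project: "The YoungFitT project is a prospective, three-arm, parallel, single-blinded RCT mixed-methods study planned to be conducted in two phases".

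The Randomization section then treats the two studies differently. For Study 1, "an independent researcher will use a software-generated random sequence to allocate participants into three groups at a 1:1:1 ratio for each wave". For Study 2, "In Study 2, participants will be assigned to one of three intervention groups through sequential cohort assignment based on recruitment order". The next sentence offers a safeguard: "Potential biases in group composition will be mitigated by monitoring baseline characteristics across groups and adjusting for these in subsequent analyses".

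Two further statements bear on what the Study 2 rule means in practice. Study status and timeline gives "three waves for Study 2 (September 2025, December 2025, and February 2026"), and adds that the schedule may vary. Sample size says: "Study 2 will include 45 participants (n = 15 per group) as part of a proof-of-concept trial intended for preliminary exploration".

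Objectives and hypotheses expects each VR intervention to show its own outcome profile, so a comparison between the VR arms is intended. It also predicts that "VR-based interventions will yield better adherence and greater benefits compared to non-VR interventions". Recruitment says participants will be told their probability of allocation to each group, without limiting this to Study 1.

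**The concern.** Assignment by order of recruitment is not randomisation. Whoever recruits or enrols can foresee the next arm, and nothing in the procedure makes the groups exchangeable apart from chance. The Study 2 text sits under the heading Randomization, in a project called an RCT throughout, so a reader of the results would take the between-arm contrasts to be randomised ones.

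The more serious possibility is that arm and recruitment wave coincide. The Recruitment section itself names exams and holidays as influences to be minimised. A 12-week programme started in September, December or February reaches its post-assessment at a different point in the academic year. If each arm occupies one wave, a seasonal change in stress, mood or test performance would appear as an intervention effect. Baseline covariates cannot absorb a calendar influence that arises after baseline.

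At stake are the between-arm VR effect sizes, which the Discussion intends as input to larger studies.

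**Working it through.** **1. The plan's own figure.** The only computed figure in the article is the Study 1 sample size. With three groups, f = 0.25 and α = 0.05, N = 159 gives noncentrality 159 × 0.25² = 9.94, critical F(2, 156) = 3.054 and power 0.805. Allowing for 10% dropout, 159 / 0.9 = 176.7, so 177. All of this reproduces and is not in question. Study 2's 45 participants carry no power calculation.

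**2. The label against the rule.** Abstract and Study design: randomised controlled trials. Randomization, Study 1: a software-generated random sequence, 1:1:1 in each wave. Randomization, Study 2: recruitment order. The Study 2 rule contains no random step on any reading, so the contradiction needs no calculation.

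**3. Can arm be separated from wave?** Take 45 participants, 3 arms of 15 and, as an assumption, 3 equal waves of 15. The model has an intercept, two arm terms and two wave terms, which is five columns.

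| Reading of the Study 2 rule | Rank of arm + wave matrix | Consequence |
|---|---|---|
| One cohort receives one arm | 3 of 5 | arm and wave fully aliased |
| Individuals rotated through arms in order | 5 of 5 | wave separable; allocation predictable and not random |

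**4. Illustrative size on the first reading.** Suppose there is no intervention effect and one cohort is shifted by s residual SDs. The three cohort means are then 0, 0 and s, and their population standard deviation is f = s√2/3. The noncentrality is λ = N f² = 45 × 2s²/9 = 10s². With three arms and three covariate degrees of freedom (baseline score, sex, age), the error df is 45 − 3 − 3 = 39 and critical F(2, 39) = 3.238.

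| Assumed shift s | λ | False-positive rate of the 5% omnibus test |
|---|---|---|
| 0.2 SD | 0.4 | 0.079 |
| 0.3 SD | 0.9 | 0.118 |
| 0.5 SD | 2.5 | 0.256 |

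**5. A second check by simulation.** There were 40,000 runs per setting, with 15 per arm, no true arm effect, random cohort effects and no covariates. The intraclass correlation between cohorts is assumed.

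| Assumed ICC | Rejection rate, one arm per cohort | Rejection rate, randomised 5 per arm per wave, wave in model |
|---|---|---|
| 0 | 0.051 | 0.049 |
| 0.02 | 0.097 | 0.050 |
| 0.05 | 0.178 | 0.051 |
| 0.10 | 0.312 | 0.050 |

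The shifts and ICCs are assumptions throughout, because the article gives no cohort effect. Both checks show the same thing: on the one-arm-per-cohort reading the error rate depends on an unknown cohort difference, and within-wave randomisation removes that dependence.

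**The case against.** The strongest reply has four parts.

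*One arm per cohort is not stated.* This stands. The text does not equate a cohort with a recruitment wave or a wave with an arm, the schedule is said to be flexible, and the study design figure is not available here. A reader might infer that every VR arm is certainly confounded with its cohort. The numbers make that the likeliest reading, but the document does not establish it, and under rotation it would be false.

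*The inflation figures have no anchor in the document.* This also stands. A reader might take 8% to 26% as an estimate of the trial's actual error rate. It is not: it shows what would follow from assumed shifts, and only on the first reading.

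*Study 2 is a proof of concept.* The article calls its findings preliminary, states the allocation method openly and concedes possible imbalance in group composition. Usability, acceptability, adherence and feasibility within each arm do not need randomised arms. This lowers the severity. It does not cure the label, because the limitation given in the Discussion is small sample size, which is a different problem from bias.

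*The comparison of VR with non-VR is separate.* This is correct. The article never calls it randomised and lists it as exploratory, and randomising Study 2 would not change it. A reader might want it confined to September 2025, when both studies recruit. That would leave either one VR arm or about five VR participants per arm, and the comparison would still not be randomised.

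**Conclusion.** The description of Study 2 as a randomised controlled trial is contradicted by its own allocation rule. This rests on explicit text and holds on every reading. Adjustment for measured baseline characteristics does not turn recruitment-order assignment into randomisation.

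The confounding of arm with calendar wave is conditional. It is complete if each cohort receives one arm, which the design numbers suggest, and absent if individuals are rotated through the arms. Its size cannot be derived from the document.

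This should be fixed, but it does not threaten the project's main result. Study 1, the powered trial with a target of 177, is randomised within wave and is unaffected.

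**What to change.** **Preferred.** Randomise Study 2 1:1:1 within each wave (5 per arm per wave if waves are equal, still 45 in total), using the same independent software-generated list as Study 1, and include wave in the Study 2 ANCOVA. The cost is an amendment and a list, with no extra participants. The real constraint is that all three VR environments, which still have to be co-designed and built, must be ready for the first wave.

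**If that is not feasible.**
- Remove the word randomised from the description of Study 2 in the abstract, Study design and Randomization, and state exactly how cohorts map to arms and waves.
- Correct the Recruitment wording on allocation probability so that it does not apply to Study 2.
- Report adjusted between-arm estimates as non-randomised and exploratory, with possible cohort confounding stated as a limitation.

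This alternative costs only text, but it gives up a randomised contrast between the VR arms.

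**In either case.** State that VR versus non-VR is a non-randomised, exploratory comparison across studies. It need not be restricted to the September 2025 wave.

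### A significant result of the blinding check cannot be read as failed blinding, because assessors guess after testing and the benchmark is the 33% rate of an uninformed guess

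*Protocol article*

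**What the plan says.** The Randomization section of the protocol article describes assessor blinding and its check in four steps.

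- Concealment: "Outcome assessors will be blinded to group allocation through the use of coded identifiers to ensure unbiased assessments".
- The threat it guards against is disclosure by participants: "participants will be reminded not to discuss their group allocation during post-intervention assessments".
- The check: "To assess blinding success, outcome assessors will guess participants’ group assignments after the final evaluation".
- The test: "The proportion of correct guesses will be compared to the 33% chance level using a chi-square goodness-of-fit test with one degree of freedom".

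Study 1 is randomised equally: "allocate participants into three groups at a 1:1:1 ratio for each wave". The Study 1 hypotheses (Objectives and hypotheses) expect improvement in every arm, "with each intervention showing a specific profile of outcomes (HIFT: more cognitive gains; MBSR: more psychological gains; QG: moderate benefits in both areas". The Sample size section plans on a between-arm difference: "Assuming a medium effect size (f = 0.25), α = 0.05, and a desired power of 0.80". Table 2 lists the cognitive and fitness tests that are measured before and after the interventions. The Cognitive functions section makes changes in the cognitive domains and in global cognition primary outcomes.

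The text mentions no guess before testing, no reason for the guess and no record of whether a group was revealed.

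**The concern.** The benchmark and the tested quantity do not match. One third is the hit rate of someone who knows nothing about the participant. The quantity tested is the hit rate of someone who may just have watched that participant perform. If performance differs by arm, as the plan predicts, results carry information about allocation, and a perfectly blinded assessor who uses them will be right more often than one time in three.

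A significant result then has two explanations, disclosure or inference from results, and the stated data cannot separate them. Blinded assessment is what protects the assessor-administered cognitive primary outcomes from assessor bias. A check that can move with the treatment effect could cast doubt on a genuine between-arm difference, and actual disclosure would remain unmeasured.

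**Working it through.** **Inputs from the protocol article.** Three arms at 1:1:1, a 33% null and a 1-df chi-square test (Randomization); f = 0.25, α = 0.05, power 0.80, N = 159, critical F 3.054, target 177 (Sample size); two-tailed 0.05 (Statistical analyses).

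**Assumptions not in the documents.** Guesses are independent; nothing is disclosed; the assessor knows the expected ordering of the arms; the assessor uses one normally distributed outcome with three equally spaced arm means. The share of guesses based on results is also assumed, and is varied below.

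**1. The plan's own figure.** One-way ANOVA with three groups and noncentrality f²N: at N = 159 the critical F is 3.054 and power is 0.805. The smallest N reaching 0.80 is 158, hence 159 when balanced. 159/0.90 = 176.7, giving 177. The sample size reproduces. The blinding check has no stated power.

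**2. Rejection region.** The statistic is (x − n/3)² / (n × 2/9), rejecting above 3.841. With n = 159, n/3 = 53 and n × 2/9 = 35.33. At x = 65 it is 144/35.33 = 4.08 (reject); at x = 64 it is 121/35.33 = 3.42 (do not reject). So 65 or more correct (40.9%) is significantly above chance. By symmetry, 41 or fewer is significantly below.

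**3. Uninformed guesses.** The exact binomial rejection probability at p = 1/3 is 0.053 (0.046 at n = 177). The test is sound for the guess it presumes.

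**4. Hit rate of a blinded assessor using one outcome.** With arm means −d, 0, +d and SD 1, f = d√(2/3), so d = f√1.5. The best cut-points are ±d/2, and the hit rate is [4Φ(d/2) − 1]/3. For f = 0.25, d = 0.306, Φ(0.153) = 0.5608, and the hit rate is (2.2434 − 1)/3 = 0.4145.

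If only a share w of guesses uses the outcome, the hit rate is w × 0.4145 + (1 − w)/3.

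**5. Baseline adjustment.** The Statistical analyses section models change scores adjusted for baseline, whereas an assessor may see only raw post-intervention scores. If f = 0.25 is the adjusted effect and r is the pre-post correlation (assumed), the effect on the raw score is f√(1 − r²): 0.217 at r = 0.5, 0.179 at r = 0.7 and 0.150 at r = 0.8.

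**6. Probability that the test rejects with nothing disclosed, n = 159.**

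| Scenario | Correct | Rejects |
|---|---|---|
| Uninformed, or arms do not differ | 33.3% | 0.05 |
| f = 0.25, every guess optimal | 41.4% | 0.59 |
| f = 0.25, half of guesses | 37.4% | 0.20 |
| f = 0.25, a quarter of guesses | 35.4% | 0.09 |
| f = 0.10, every guess | 36.6% | 0.15 |
| Raw scores, r = 0.5, every guess | 40.4% | 0.48 |
| Raw scores, r = 0.7, every guess | 39.1% | 0.35 |
| Raw scores, r = 0.8, every guess | 38.2% | 0.27 |

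A simulation of the f = 0.25 case with 53 per arm gave 41.5% correct and 0.60 rejection; with no difference between arms it gave 33.3% and 0.04.

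**The case against.** Several objections have force.

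- **No pass/fail rule is written.** The section only compares the proportion with 33%. Nothing in Statistical analyses uses the result, so no treatment estimate or error rate of the trial depends on it. This stands and limits the consequence to interpretation. The stated purpose is nevertheless to judge blinding success, and a significant result would naturally be read that way.
- **The 0.59 is a best case for the guesser.** It needs every guess to follow the optimal cut-points with the ordering known. No text says that assessors know the hypothesised profiles or guess from scores. With partial use, or if f is a baseline-adjusted effect and only raw scores are seen, the figure is much lower. This stands.
- **Part of the predicted profile may be invisible.** The psychological gains are measured by questionnaires that assessors may never see. The cognitive and fitness tests are enough for the argument.
- **Details of the guess may sit in the full protocol.** The basis of a guess is form-level detail that an article may omit. The timing and the benchmark, however, are stated here, and those are what clash.

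A reader might infer more than the documents support, in three ways. First, that any effective intervention breaks the check: all arms are active, and equal benefit leaves the hit rate at 33%, so the effects must differ between arms. Second, that the trial is likely to report failed blinding: how far assessors infer from results is unknown, and the plausible range runs down to nearly the nominal level. Third, that a similar figure applies to Study 2: its arms are filled by sequential cohorts in recruitment order, so timing may itself reveal the arm, and a calculation with results as the only cue does not fit.

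**Conclusion.** The concern holds as a fault of interpretation. The 33% null and the test are correct for uninformed guesses, but the guess is taken when it may be informed by the outcomes. If the arms differ as the plan predicts, and assessors can perceive and use the difference, exceeding 33% is compatible with intact blinding, so a significant result cannot be read as blinding having failed.

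For Study 1, with one informative outcome, the probability of such a result without disclosure lies between about 0.09 and at most 0.59, against about 0.05 intended. Where it falls depends on the share of outcome-based guesses, the size of the between-arm effect and whether raw or adjusted differences are visible, none of which the documents settle. The primary treatment analysis is unaffected. What is affected is what the trial can say about the blinding of its cognitive assessments.

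**What to change.** For the waves not yet assessed:

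1. Have the assessor record a guess when the participant arrives for the post-intervention visit, before any test, and compare that guess with 1/3.
2. Keep the end-of-visit guess. An arrival guess alone would miss disclosure during the visit, which is the threat that the section names.
3. At the end of the visit, add an item on whether and how the group was revealed, and on what the guess rests.
4. Report end-of-visit guesses and disclosures by arm, described as possibly outcome-informed and not as a pass/fail test of blinding.
5. Optionally, repeat the cognitive ANCOVA without participants whose group was disclosed. Label it a sensitivity analysis outside the intention-to-treat analysis, since it selects on an event after randomisation.

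The cost is one or two items on the assessor form, an earlier recording point and, if wanted, one extra analysis; no additional participants are needed. Recruitment began in February 2024, so waves already assessed have only the post-testing guess and should be reported separately. Disclosure will rest on the assessors' own reports.
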